### Concomitant medication

Cyclosporine A, mycophenolate mofetil, and short-term methotrexate for aGVHD prophylaxis will be administered. Subjects may be given antibiotics to prevent or treat infections that occur after transplantation. In addition, subjects will be able to receive supportive therapy. No other trial agents or MSC products will be allowed within 30 days prior to and during the trial.

### Sample size

This study is an exploratory study, so the sample size will not take into account the power associated with statistical hypotheses. Forty randomized subjects in each group will be included in the statistical analysis. Assuming a 20% dropout rate, we plan to enroll 96 subjects (48 in each group).

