## Methods

### Trial design

This is a multicenter, randomized, double-blind, placebo-controlled, superiority, phase II trial (Chinese Clinical Trial Registry, ChiCTR2000035740) that will enroll patients with grade II–IV steroid-refractory aGVHD from 8 Chinese centers. The primary endpoint is the overall response rate (ORR) at day 28. A total of 96 patients will be randomly assigned at a 1:1 ratio to receive either MSCs or placebo in a double-blinded manner. To ensure the interests of the patients, both the MSC and placebo groups will receive conventional second-line therapy. The MSC group will receive an infusion of hUC-MSC PLEB001 at 1.0 × 10^6^ MSC/(kg of subject, adjusted body weight) twice a week for 4 weeks. The control group will receive placebo treatment at the same frequency. The treatment efficacy will be assessed on the 28th day after the first infusion in all patients. The treatment will be terminated if the patient reaches complete response (CR), no response (NR), or progression of disease (PD) on the 28th day. Patients who display PR at day 28 will receive further infusions twice per week for an additional 4 weeks. The total treatment period will last no more than 8 weeks.

The conventional second-line therapy for patients with steroid-refractory aGVHD includes basiliximab, ruxolitinib, mycophenolate mofetil, methotrexate, etc. Investigators from each center will ensure the consistency of indications, category, and administration of second-line therapies. If deterioration or rapid progression of aGVHD is observed, another second-line agent can be added to the trial treatment regimen.

The protocol and the proposed informed consent form (ICF) will be reviewed and approved by an independent ethics committee (EC) before the study starts. Eligible patients may only be enrolled in the study after providing written informed consent.

In addition, peripheral blood samples will be collected from patients for the detection of Treg and Th17 cell populations prior to and after the treatment. Additional consent for peripheral blood sample collection and detection will also be included in the informed consent form.

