### Statistical analysis

All analyses will be carried out according to a predetermined statistical analysis plan by utilizing SAS 9.4. Two-tailed tests will be used for most statistical tests, and a *p* value of less than 0.05 will be considered statistically significant. Comparisons between groups for quantitative data will be performed by the independent samples *t* test or Wilcoxon rank sum test. Comparisons between groups of categorical data will be performed by the chi-square test or Fisher’s precision probability test. Comparisons between groups of ranked data will be performed by the Wilcoxon rank sum test or CMH test.

The full analysis set (FAS) is the set of subjects identified according to the intention-to-treat (ITT) principle. It includes all patients who have received at least one dose of study treatment after randomization. The per-protocol set (PPS) consists of the subjects in the FAS who meet the requirements of the trial and are in good compliance. The formula for calculating the adherence of subjects is as follows: adherence rate = (actual infusion dose during follow-up/planned infusion dose) × 100%. Good compliance is defined as ≥ 80% adherence rate. The safety set (SS) includes all patients who received at least one dose of study treatment. The primary and secondary efficacy analyses will be based on both the FAS and PPS. Subjects who present with protocol nonadherence will be analyzed in the FAS and SS.

Adverse events, laboratory tests, symptoms, signs, and the association between adverse events and the trial drug are presented in the form of a table.

The missing values of the primary endpoint will be processed by worst observation carried forward (WOCF). The other missing values will be analyzed on the actual observed data.

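### Minor arithmetic error: 48 enrolled per group with 20% dropout leaves about 38 per group, not the stated 40

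*Protocol article*

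**What the plan says.** The Sample size section of the protocol article gives no power calculation. It calls the study exploratory and says that "the sample size will not take into account the power associated with statistical hypotheses". It then gives a target for the analysis, "Forty randomized subjects in each group will be included in the statistical analysis", and an enrolment figure derived from it: "Assuming a 20% dropout rate, we plan to enroll 96 subjects (48 in each group").

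The Trial design section repeats the enrolment figure as a number randomised: "A total of 96 patients will be randomly assigned at a 1:1 ratio". The abstract does the same.

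Two statements in the Statistical analysis section determine who counts as analysed. Of the full analysis set (FAS) it says: "It includes all patients who have received at least one dose of study treatment after randomization". On incomplete outcomes it says: "The missing values of the primary endpoint will be processed by worst observation carried forward (WOCF"). All other missing values are left missing, and those endpoints are analysed as observed. The per-protocol set (PPS) is the part of the FAS that meets the trial requirements with at least 80% adherence. Efficacy is analysed in both sets.

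**The concern.** Two consecutive sentences give a target, a loss rate and an enrolment figure, and any two of them fix the third. The enrolment figure printed is not the one that the other two imply. A dropout rate is ordinarily a share of those enrolled, and nothing in the article defines the 20% differently.

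Because the plan disclaims power, this short calculation is the only numerical support given for the size of the trial. Someone who relies on 40 evaluable subjects per group will expect slightly more data than the plan's own dropout assumption provides.

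**Working it through.** **Inputs, all from the Sample size section:** analysed target 40 per group (80 in total); dropout d = 20%; enrolment 48 per group (96 in total).

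**1. Reproducing the plan's figure.** The stated enrolment is obtained exactly by n × (1 + d):
- per group: 40 × 1.20 = 48
- in total: 80 × 1.20 = 96

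**2. Standard inflation.** If a share d of those enrolled is lost, the number to enrol is n / (1 − d):
- per group: 40 / 0.80 = 50
- in total: 80 / 0.80 = 100, which is 4 more than planned (4/96 = 4.2%)

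**3. What the planned enrolment leaves at 20% dropout:**
- per group: 48 × 0.80 = 38.4, a shortfall of 40 − 38.4 = 1.6 (1.6/40 = 4%)
- in total: 96 × 0.80 = 76.8, a shortfall of 80 − 76.8 = 3.2

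**4. Dropout rate at which 48 does leave 40:** 1 − 40/48 = 16.7%.

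**5. Can another reading reconcile the figures?**
- Rounding cannot: 38.4 rounds to 38, or to 39 if rounded up.
- Loss before randomisation cannot: the abstract and the Trial design section have all 96 randomised.
- Taking the 20% as a share of the 40 retained would work (8/40 = 20%), but the article does not say this and it is not what a dropout rate normally means.

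**6. Effect on precision.** The plan attaches no precision to the 40, so this only illustrates the size of the error. The width of a confidence interval for a difference in response rates scales with 1/√n, so 38.4 instead of 40 widens it by √(40/38.4) = 1.02, about 2%, whatever the response rates. The article gives no assumed rates. Taking 50% in both groups, where the interval is widest, the 95% half-width 1.96 × √(2 × 0.25/n) is:

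| n per group | Half-width (percentage points) |
|---|---|
| 38.4 | 22.4 |
| 40 | 21.9 |
| 48 | 20.0 |

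**7. Which analyses are affected?** A subject who drops out after a first dose stays in the FAS, and a missing day-28 response is imputed. Only subjects randomised but never dosed leave the FAS. It would fall below 40 in a group only if more than 48 − 40 = 8 of the 48 were never dosed. Later dropout reduces the PPS and those secondary endpoints that are analysed as observed.

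**The case against.** The strongest case on the other side is that the error has almost no consequence. The article says that the size is not based on power, and it ties no precision or decision threshold to 40. A loss of 1.6 per group therefore breaks no stated operating characteristic. The FAS analysis of the primary endpoint will probably hold more than 40 per group, since every dosed subject stays in and the inclusion criteria require that treatment can start within 3 days of enrolment. The enrolment figure of 96 is used consistently throughout. All of this stands, and it is why the point is minor.

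It can also be said that no formula is shown, so a multiplied-on allowance is an inference, and that 20% may be loose wording for a margin added on top of 40. The first part is right: the exact match to 40 × 1.2 makes the inference likely but does not prove it. The second part does not rescue the text, which calls the 20% a dropout rate and gives no other denominator.

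A reader might go further and infer that the 40 analysed contradicts the FAS definition. The documents do not support that. The Sample size section does not name the analysis set it has in mind, and the figure can be read as the PPS, one of the two efficacy sets. An unnamed set is an ambiguity, and the full protocol or the analysis plan may resolve it.

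**Conclusion.** The statement is wrong as written, but the error is minor. The figures of 40 analysed, 20% dropout and 48 enrolled per group cannot all hold. At 20% dropout, 48 leaves about 38 per group (77 in total). Forty from 48 corresponds to 16.7% dropout, and 40 at 20% dropout would need 50 per group (100 in total). This rests on one assumption, that the 20% is a share of those enrolled.

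The shortfall is 1.6 per group, about 3 subjects overall, and it falls mainly on the PPS and the observed-data analyses.

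Two stronger conclusions might be drawn, and neither is supported. The first is that the trial loses power or that its primary analysis falls short. No power is stated, and the FAS with imputation keeps every dosed dropout in the primary analysis. The second is that 100 patients must be enrolled. Nothing in the plan depends on reaching exactly 40, so correcting the sentence is enough.

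**What to change.** Keep 96 and correct the sentence in the Sample size section in one of two ways:
- 96 subjects will be enrolled (48 per group); with 20% dropout, about 38 per group (77 in total) are expected to be evaluable; or
- 96 subjects will be enrolled (48 per group), which allows for 16.7% dropout with 40 evaluable per group.

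In either case add one sentence saying that this number refers to evaluable (per-protocol) subjects, and that the FAS includes all dosed subjects, up to 48 per group. The sponsor should confirm that this is the set that was meant. Any full protocol or analysis plan that repeats the calculation should carry the same wording.

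The cost is one or two sentences. No patients are added, which matters because the Trial status section already reports 78 recruited, and no analysis changes. The first option states a slightly less favourable evaluable number; the second states a slightly smaller dropout allowance.

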### Data collection and management

An electronic data management center (EDC) will be used in this trial for data collection, with reliable retention of audit recording and effective management of account privileges. The case report form (CRF) will be designed based on the trial protocol, and the electronic case report form (eCRF) will be created in the EDC. The medical record and original transcript will be preserved and scanned to perform an electronic backup as the source documents for 30 years.

Investigators will be required to collect data on subjects according to Good Clinical Practice (GCP) and study protocol requirements. The investigator will enter the data into the EDC system and preserve it in accordance with the eCRF guidelines.

### Statistical analysis

All analyses will be carried out according to a predetermined statistical analysis plan by utilizing SAS 9.4. Two-tailed tests will be used for most statistical tests, and a *p* value of less than 0.05 will be considered statistically significant. Comparisons between groups for quantitative data will be performed by the independent samples *t* test or Wilcoxon rank sum test. Comparisons between groups of categorical data will be performed by the chi-square test or Fisher’s precision probability test. Comparisons between groups of ranked data will be performed by the Wilcoxon rank sum test or CMH test.

The full analysis set (FAS) is the set of subjects identified according to the intention-to-treat (ITT) principle. It includes all patients who have received at least one dose of study treatment after randomization. The per-protocol set (PPS) consists of the subjects in the FAS who meet the requirements of the trial and are in good compliance. The formula for calculating the adherence of subjects is as follows: adherence rate = (actual infusion dose during follow-up/planned infusion dose) × 100%. Good compliance is defined as ≥ 80% adherence rate. The safety set (SS) includes all patients who received at least one dose of study treatment. The primary and secondary efficacy analyses will be based on both the FAS and PPS. Subjects who present with protocol nonadherence will be analyzed in the FAS and SS.

Adverse events, laboratory tests, symptoms, signs, and the association between adverse events and the trial drug are presented in the form of a table.

The missing values of the primary endpoint will be processed by worst observation carried forward (WOCF). The other missing values will be analyzed on the actual observed data.

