**Methods:**

This is a clinical trial protocol for a multicenter, randomized, double-blind, placebo-controlled phase II study. The aim of the trial is to evaluate the efficacy and safety of the administration of the human umbilical cord-derived MSC product hUC-MSC PLEB001 in patients with grade II–IV, steroid-refractory aGVHD. A total of 96 patients will be randomized 1:1 to receive MSC or placebo treatment twice per week for 4 weeks, in addition to second-line therapy according to institutional standards. Patients who achieve partial response (PR) at day 28 will be eligible to receive further infusions twice per week for an additional 4 weeks.

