Hence, there is an urgent need for randomized controlled trials (RCTs) to confirm the effect of MSCs on steroid-refractory aGVHD. By December 2021, nine RCT studies had been registered on ClinicalTrials.gov or the WHO’s international clinical trial registration platform (ICTRP) [18]. In 2020, Kebriaei et al. reported a multicenter, randomized, phase 3, double-blind, placebo-controlled trial of MSCs for 260 steroid-refractory patients [19]. The study failed to meet its primary endpoint—there was no significant difference between the durable complete response (DCR) rate in patients treated with MSCs in comparison to those treated with placebo (35% vs. 30%, *p* = 0.42). The trial found that MSC treatment led to significantly improved overall response (OR, 55% vs. 26%, *p* = 0.05) and DCR rates (29% vs. 5%, *p* = 0.047) in patients with liver aGVHD. There was also a higher overall response rate in children treated with MSCs than in controls (64% vs. 23%, *p* = 0.05). However, this study design involved both pediatric and adult patients, leading to clinical heterogeneity. Another limitation of the study was the nonstandardized use of second-line agents across study units.

Therefore, we designed a prospective, randomized, double-blind, placebo-controlled, multicenter phase II clinical trial to evaluate the efficacy and safety of the human umbilical cord-derived MSC product hUC-MSC PLEB001 in patients with grade II–IV steroid-refractory aGVHD.

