### Study setting

The study will be conducted in 8 hematopoietic stem cell transplantation centers in China, including the First Medical Center of Chinese PLA General Hospital; the Fifth Medical Center of Chinese PLA General Hospital; Institute of Hematology & Blood Disease Hospital, Chines Academy of Medical Sciences & Peking Union Medical College; Shandong Provincial Hospital Affiliated to Shandong First Medical University; the Second Hospital of Hebei Medical University; the First Affiliated Hospital of Zhengzhou University; Henan Provincial People’s Hospital; and the Affiliated Hospital of Xuzhou Medical University, which are highly experienced in the management of GVHD and hematopoietic stem cell transplantation with routine patient education about clinical trials.

This study started in June 2020, and patients will be recruited over the course of 2 years. Each study site will use the newly diagnosed aGVHD patient list to identify and recruit potential subjects. Recruitment videos and advertisements for potential subjects will be advertised among patients through their doctors. If a patient intends to enter the study, dedicated staff will meet with the patient face-to-face, give more detail to introduce the study, and arrange the appropriate screening procedures.

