### Study endpoints

This trial aims to assess the efficacy and safety of hUC-MSC PLEB001 in patients with grade II–IV steroid-refractory aGVHD. The primary endpoint is the overall response rate (ORR) at day 28, which is defined as the proportion of patients achieving a CR or PR without the use of additional systemic therapies for aGVHD. The secondary endpoints include the CR rate at day 28, ORR at day 56, CR rate at day 56, durable ORR at day 56, DCR, OS, and Eastern Cooperative Oncology Group (ECOG) score. The safety endpoints include adverse events (AEs), serious adverse events (SAEs), and infusion toxicity (Table 2).

**Table 2 Tab2:** Study endpoints

Aim	Indicator
Primary endpoint	ORR at day 28
Secondary endpoints	CR at day 28, day 56
	ORR at day 56
	Durable ORR at day 56
	DCR within day 100
	OS at day 100, day 180
	ECOG score at day 28, day 56, day 100
Safety endpoints	AE/SAE at day 180
	infusion toxicity at day 14

1. Complete remission (CR): absence of any aGVHD-related symptoms

2. Partial remission (PR): an improvement in severity of at least 1 stage in all initial organs without further deterioration of other organs

3. No response (NR): the absence of improvement or deterioration of symptoms in any organ or death

4. Progressive disease (PD): a deterioration in the severity of at least 1 stage in a single organ with or without improvement in other organs

5. Overall response rate (ORR) = CR + PR

6. Durable ORR: the percentage of subjects who achieve CR + PR on day 28 and remain CR + PR on day 56

7. Durable complete response (DCR): complete resolution of aGVHD symptoms for at least 28 days within 100 days after the first infusion

8. Infusion toxicity includes fever, phlebitis, headache, dizziness, nausea, chest pain, shortness of breath, transient pulmonary edema, allergic reaction, skin rash, injection site pruritus, etc.

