### Randomization and double-blind design

To reduce the possible selection bias and efficacy evaluation bias from investigators and subjects, this trial will adopt a randomized, double-blind, placebo-controlled design. Since the baseline treatment is the current standard treatment regimen, this study will adopt a loading design, which meets the ethical requirements.

The multicenter subblock randomization method will be used, and a random number table will be generated by professional statisticians using SAS (version 9.4) software. The subjects will be randomly allocated, and the investigational drugs will be allocated in the Central Randomization System of Clinical Information Management System (CIMS-CRS).

After signing the informed consent form, each subject will be given a screening number. The length of the screening number is N, and the naming rule is “S” + center number (XX) + sequence number (XXX). The random number is obtained after successful randomization, the length of the random number is N, and the naming rule is N-digit natural number (XXX).

In this trial, CIMS-CRS will be connected with the Alibaba Health precision traceability system to complete drug blinding. The unique tracking numbers for investigational drug distribution are generated by the drug management module of the Alibaba Health precision traceability system. The two systems work together to accurately manage and fully trace investigational drugs and clinical data.

A unique traceability code on the subject’s medication bag must be recorded using a code scanner prior to use of all medications. Normally, blinding should not be broken until all subjects have completed the study and the database is locked. To ensure the double-blind design, a light-protected infusion set will be used to shield the investigational product.

If severe safety issues arise in the study that requires the investigator to know the subject’s group, an unblinding procedure should be initiated. An emergency unblinding license will be generated in the center system, which permits the investigators and subjects to check their grouping. Immediately upon unblinding, the sponsor and the contract research organization need to be notified. Information about unblinding should be recorded in the subject’s source documentation and electronic medical record.

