## Discussions

MSCs inhibit the progression of aGVHD through their immunomodulating activities, and many clinical studies have investigated the potential of MSCs as a treatment option for steroid-refractory aGVHD. However, most of the data are from retrospective or uncontrolled trials with heterogenous indications and procedures [17, 21]. We designed a multicenter, double-blind, randomized, placebo-controlled, phase II study of the umbilical cord-derived mesenchymal stem cell product hUC-MSC PLEB001 for steroid-refractory aGVHD. This study aims to answer two important questions: whether the umbilical cord-derived MSC product hUC-MSC PLEB001 is tolerable and safe in patients with aGVHD after allo-HSCT and whether patients suffering from steroid-refractory aGVHD can benefit from MSC-based treatment.

Most clinical trials focus on steroid-resistant aGVHD; on the other hand, steroid-dependent aGVHD, which is experienced by approximately 30% of patients with aGVHD [22], is ignored. Steroid-dependent aGVHD is associated with morbidity and a prolonged health care burden. In this study, we planned to enroll patients with steroid-refractory aGVHD, which includes both steroid-resistant aGVHD and steroid-dependent aGVHD. Therefore, this strategy of subjective enrollment makes the current trial more comprehensive and practical in the clinical setting.

Bone marrow is the most common source of MSCs in both academic research and commercial application [17, 23]. However, the invasive procedure of bone marrow collection limits its clinical application. Recently, umbilical cord-derived MSCs have gained more attention for their simple availability and low immunogenicity [24]. With potential immunomodulatory activity and stability similar to those of BM-derived MSCs [25], umbilical cord-derived MSCs have been shown to promote engraftment and reduce the incidence of cGVHD [26].

To date, no therapy has yet been established as an optimal second-line treatment for aGVHD. Mesenchymal stem cells have shown substantially promising results in the last two decades. However, solid evidence from high-quality studies is still lacking. This clinical trial will provide additional high-quality evidence for the clinical application of MSCs in the future.

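### The only tests named for a binary endpoint such as day-28 ORR are unstratified, although randomisation is blocked across centres and baseline aGVHD grade is collected

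*Protocol article*

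**What the plan says.** The primary endpoint is binary: "The primary endpoint is the overall response rate (ORR) at day 28, which is defined as the proportion of patients achieving a CR or PR" (Protocol article, Study endpoints).

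The Statistical analysis section assigns tests by type of data. For categorical data: "Comparisons between groups of categorical data will be performed by the chi-square test or" Fisher's exact test. For ordered data: "Comparisons between groups of ranked data will be performed by the Wilcoxon rank sum test or CMH test". No test is tied to ORR by name, and the section refers to a predetermined SAP that is not shown.

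On allocation, Randomization and double-blind design says "The multicenter subblock randomization method will be used". Grade is not mentioned as a balancing factor. Study setting says "The study will be conducted in 8 hematopoietic stem cell transplantation centers in China". Table 1 schedules an aGVHD evaluation at screening by the modified Glucksberg criteria, so baseline grade is available for every randomised patient.

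The population is mixed. It spans grades II to IV, and the Discussions section says "we planned to enroll patients with steroid-refractory aGVHD, which includes both steroid-resistant aGVHD and steroid-dependent aGVHD". Background therapy is given "in addition to second-line therapy according to institutional standards" (Abstract, Methods).

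**The concern.** A test family is stated for the kind of data that ORR is, and it is unstratified. The one stratified procedure in the section is assigned elsewhere. Two consequences follow.

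- **Grade.** Nothing described balances grade between arms. At this size a visible chance imbalance is not rare, and the stated test cannot correct it. An adjustment chosen after seeing the imbalance unblinded would be post hoc.
- **Centre.** If blocks are formed within centre, the design removes between-centre variation from the treatment comparison, but the crude test still counts that variation in its standard error. The test is then conservative to the extent that centres differ. Differences are plausible: the Background criticises an earlier trial in the words "Another limitation of the study was the nonstandardized use of second-line agents across study units", and this trial also permits several agents.

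At stake are some power and a defensible primary result if the arms turn out unequal in severity.

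**Working it through.** **The plan's own figures.** The 96 reproduces as 40 × 1.2 × 2. No power, effect size or control ORR is stated, so there is no planned power to reproduce. I use 48 per arm throughout.

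**Imbalance in grade.** Assume half the patients are grade III–IV. The SD of the between-arm difference in that share is √(2 × 0.5 × 0.5 / 48) = 0.102, or about 10 points. About 5% of trials exceed 1.96 × 10.2 = 20 points. At 40 per arm the SD is √(2 × 0.25 / 40) = 11.2 points.

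The shift in the crude ORR difference is the imbalance times the ORR gap between grades. With an assumed gap of 30 to 45 points, a 10-point imbalance moves it by 3.0 to 4.5 points, and a 20-point imbalance by 6 to 9 points.

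**Test compared.** The CMH statistic is [Σ(aₖ − n₁ₖm₁ₖ/nₖ)]² / Σ[n₁ₖn₀ₖm₁ₖm₀ₖ / (nₖ²(nₖ − 1))], referred to 3.84. In stratum k, nₖ is the number of patients, n₁ₖ and n₀ₖ the numbers per arm, m₁ₖ and m₀ₖ the responders and non-responders, and aₖ the responders on MSC.

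**Simulation.** From the article: 96 patients, 1:1, 8 centres, two-sided 5%. Assumed: 12 patients per centre, blocks of 4 within centre, half grade III–IV, normal centre effects on the logit scale, treatment log odds ratio 1.0, and control ORRs as shown (at a centre with zero effect). There were 20,000 trials per row. Power in %:

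| Centre SD | Control ORR II / III–IV | Crude | CMH grade | CMH centre | 4 centre groups × grade | 8 centres × grade |
|---|---|---|---|---|---|---|
| 0 | 65 / 20 | 49.0 | 56.8 | 49.1 | 55.6 | 53.1 |
| 0 | 60 / 30 | 58.8 | 62.1 | 58.9 | 60.5 | 58.3 |
| 0 | 55 / 35 | 64.0 | 65.1 | 64.2 | 63.8 | 61.4 |
| 0 | 45 / 45 | 66.7 | 66.3 | 66.8 | 64.5 | 62.3 |
| 1.0 | 65 / 20 | 41.1 | 46.6 | 45.2 | 47.4 | 49.0 |
| 1.0 | 60 / 30 | 48.1 | 50.0 | 53.8 | 50.7 | 52.8 |
| 1.0 | 55 / 35 | 50.4 | 50.8 | 56.2 | 52.0 | 54.0 |
| 1.0 | 45 / 45 | 52.1 | 51.3 | 58.2 | 52.5 | 54.5 |

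- Grade alone: −0.8 to +7.8 points against crude.
- Centre alone: about 0 to +6 points.
- All 8 centres crossed with two grade levels: down 4.4 points when neither factor matters (66.7 to 62.3), up when centres differ strongly.

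**Type I error, no treatment effect.** At centre SD 0 the crude test rejects in 4.7–5.3% of trials. At SD 1.0 it rejects in 3.2–3.9%, CMH by centre in 4.8–5.1%, the four-group version in 3.9–4.3%, and CMH by grade alone in 3.2–3.5%. Grade alone therefore does not remove the conservatism that comes from centres.

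**Trials with a visible imbalance.** The grade III–IV shares differ by 15 points or more in 12–13% of trials. Among those, with no treatment or centre effect, the crude test rejects in 11.9% (ORR 65/20) and 8.9% (60/30). CMH by grade rejects in 4.8% and 5.0%.

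**Second set of assumptions.** With ORR 40% vs 65%, three grade levels and 10,000 trials per scenario, at 48 per arm CMH by centre gains 0 to 5 points. CMH by grade runs from −1.5 (71.9% to 70.4%) to +5.1 (70.4% to 75.5%). Crossing 8 centres with three grades (24 strata) costs up to 9.1 points (69.7% to 60.6%), and up to 12.7 at 40 per arm (63.8% to 51.1%).

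**The case against.** The strongest reply is that the article defers to an SAP, lists tests only by data type and leaves covariates to that SAP. This stands in part: an adjusted primary analysis there cannot be excluded. But the article is not silent. It names an unstratified family for categorical data and confines CMH to ranked data, so the text at least needs aligning.

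Centre stratification is inferred from the phrase on multicentre blocks and is not stated outright. That also stands. If the inference is right, centre imbalance is already limited by design, so the imbalance argument concerns grade only.

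A reader might infer that the crude test is invalid or inflates false positives. It does not: averaged over randomisations its error rate is about 5% or lower. The 9–12% rejection rates apply only to trials already known to be imbalanced, under strongly prognostic grade.

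A reader might also infer that the trial misses its power. The Sample size section calls the study exploratory and sets no power target, so nothing stated is missed. The test still carries weight, because Trial design calls this a superiority trial and p < 0.05 is the criterion.

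Finally, a reader might take the remark on the earlier trial's second-line agents as a contradiction of this trial's own practice. Trial design asks investigators to keep indications, category and administration consistent, so the documents show only that centre differences remain plausible.

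**Conclusion.** The point holds as a matter of efficiency and robustness, not validity. The article's stated tests for a binary endpoint ignore the apparent centre blocks and a baseline grade already collected. The benefit of using them is modest and conditional: about 0 to +8 points of power for grade, about 0 to +5 or +6 for centre, and protection against a grade imbalance that has an SD of about 10 points. These sizes rest on assumed ORRs by grade, an assumed grade mix, equal centres and an assumed centre SD, none of which the article gives. With weakly prognostic factors the gain is nil or slightly negative. The claim that the crude test necessarily loses power is not supported, nor is the idea that more strata are always better.

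**What to change.** Before unblinding, name one primary test for day-28 ORR: a two-sided CMH with few strata, reported with the Mantel–Haenszel risk difference and 95% CI. Either of these is reasonable:

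- baseline grade (II vs III–IV) crossed with centres pooled into a few groups by a rule fixed in advance; or
- grade alone, with centre in a sensitivity logistic model.

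Keep the crude chi-square as supportive. Do not cross all 8 centres with grade. Leave the second-line agent out of the model unless it was recorded before randomisation; the article describes no such record.

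Naming one test also closes the open choice between chi-square and Fisher. At 48 per arm and an assumed 40% vs 60%, that choice is worth 51.1% − 42.8% = 8.3 points of power.

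The cost is SAP wording, a centre-pooling rule, and a possible loss of about 2 points with four centre groups (under 1 with grade alone) if neither factor is prognostic. No new data are needed. The article keeps the blind until database lock, so the change is clean only if made before then; after that, the adjusted analysis should be labelled post hoc. If the SAP already adjusts, revise the Statistical analysis section to match.
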